## Aims and objectives

### Aim

To test the feasibility of a multi-component behaviour change intervention aimed at increasing physical activity and reducing sedentary behaviour compared with a one-off education session in people with SMI living in rural and semi-rural locations.

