### Study population

This trial aims to recruit 60 participants: 30 in the intervention group and 30 in the control group. A formal sample size calculation was not used for this feasibility study; it is anticipated that this sample size will provide sufficient information on the study objectives to inform a future main trial. The inclusion criteria will be adult participants (male or female; aged ≥ 18 years) with a diagnosis of any SMI (schizophrenia, psychosis, bipolar disorder and major depression), not meeting the national physical activity guidelines. A validated questionnaire, the General Practice Physical Activity Questionnaire (GPPAQ), will be used to screen physical activity levels [25]. Exclusion criteria will be those with significant movement impairment, those identified as ‘Active’ using the GPPAQ screening tool and those unable to understand English or who lack comprehension to understand the purpose of the study and give written informed consent. The revised Physical Activity Readiness Questionnaire (PAR-Q) [26] will be used to identify any health-related risks of exercising that would require a participant to consult their general practitioner prior to changing their physical activity levels.

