
**Fig. 3 Fig3:**
[figure not shown]
SPIRIT schedule of enrolment, intervention and assessment

At baseline, socio-demographic information will be collected, including age, gender, ethnicity, living arrangements, pain level, smoking status, psychiatric diagnosis and current medications. Additionally, at baseline, all participants complete the Montreal Cognitive Assessment (MoCA) [41], a 30-item screening tool that is validated in SMI [42] and examines cognitive domains including executive functioning, attention and verbal fluency. Scores < 26 are suggestive of cognitive impairment. This data will be used to understand the implications of cognitive impairment on intervention delivery and completion of outcome assessments.

For the post-intervention assessment, attempts will be made to follow all participants, including those who discontinue the intervention early. Follow-up assessments at 6, 12, 18 and 24 months will be optional and will include the outcomes summarised in Fig. 3. Additionally, information on participants’ continuation with intervention components after the end of the programme will be collected.

Process evaluation (study objective IV): In addition to the outcome assessment, a qualitative process evaluation will be conducted to explore participants’ experience of the intervention, factors influencing engagement with the intervention and intervention changes required. Qualitative data from semi-structured interviews will be considered alongside the BREQ-2 and PNSE measures to consider how motivational constructs may mediate the effects of the intervention on behaviour change.

The process evaluation will also explore how the clinicians delivering the coaching intervention experienced this; qualitative data collection will explore their ability to deliver the instructions as planned, including facilitators and barriers to the delivery, the sufficiency of the training and the support from the research team. Members of the wider mental health care team who are involved in supporting participants with aspects of the intervention will also be invited to a focus group, dyad or interview (depending on the availability of individuals) to explore the level of support required by participants and the challenges and facilitators to complete the intervention from their perspective.

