### Data analysis

Statistical analysis will be performed using SPSS software. The data will be checked for normality, then appropriate descriptive analyses will be used to summarise participant characteristics and outcomes. Feasibility, the primary outcome of this study, will be evaluated by calculating the percentage of people approached who participate in the intervention (recruitment) and the percentage who complete the intervention (retention and adherence).

As this is a feasibility study, significance tests will not be performed on secondary outcomes, such as change in anthropometric measures, physical activity or sedentary time. Intervention effects will be represented by point estimates and their standard deviations. Point estimates will be calculated by subtracting unadjusted mean data at each post-intervention timepoint from the mean data at the baseline timepoint. These will be used along with their standard deviations to estimate a sample size required for a definitive trial, if appropriate [45].

Qualitative data from interviews, dyads and focus groups will be transcribed verbatim, and interpretation, synthesis and data reduction will be undertaken independently by two members of the research team to identify relevant themes. Qualitative findings will be used alongside quantitative outcomes related to process evaluation (BREQ-2 and PNSE) to understand how the intervention was experienced by participants and any changes that they think would improve the intervention.

The traffic light system [46] will be used to guide progression to a main trial, as recommended in recent best practice, and will use the worst performing of the four elements in Table 1 to select which of the following actions to take:

**Table 1 Tab1:** Criteria for progression to main trial

	Red	Amber	Green

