**Signal of efficacy**			
**Results for primary clinical outcome and safety**	CI for effect estimate for primary clinical outcome that does not include a clinically important difference or evidence of significant harm	CI for effect estimate for primary outcome that is mostly negative or evidence of potential harm	CI for effect estimate for primary outcome that is mostly positive and no evidence of potential harm

**Green**: progress to main trial with a review of screening logs and protocol to address any barriers to recruitment, adherence or retention.

**Amber**: progress to main trial after discussion with Trial Steering Committee/Trial Management Group with a full review of screening logs and protocol deviations to implement solutions to barriers to recruitment, adherence or retention, and (if relevant) a review of feedback from participants and clinicians, and (if relevant) reconsideration of the intervention.

**Red**: probably not progress to main trial without substantial changes.

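### The intervention effect is defined as baseline mean minus follow-up mean, with no contrast between arms, and this figure is carried into the main-trial sample size

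*Protocol article*

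**What the plan says.** The relevant rule is in the Data analysis section of the protocol article. It first states that "Intervention effects will be represented by point estimates and their standard deviations". The next sentence says how: "Point estimates will be calculated by subtracting unadjusted mean data at each post-intervention timepoint from the mean data at the baseline timepoint". A third sentence uses these estimates and their standard deviations to size a definitive trial, where appropriate.

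The Aim is comparative. The intervention is "aimed at increasing physical activity and reducing sedentary behaviour" and is to be "compared with a one-off education session in people with SMI living in rural and semi-rural locations". Objective iii and the description of the accelerometer outcome speak of change only and name no contrast between arms.

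Table 1 (criteria for progression) has an efficacy row. Its Green level requires a "CI for effect estimate for primary outcome that is mostly positive and no evidence of potential harm"; Amber is the mirror image, with an interval lying mostly on the negative side. The contrast and the favourable direction are not stated there. Progression follows the worst of the four rows.

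Under Secondary outcomes, "Follow-up assessments at 6, 12, 18 and 24 months will be optional".

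**The concern.** In a randomised trial the effect of the intervention is a difference between arms. The rule instead defines a difference between two times, and nothing in it removes change that would have happened anyway.

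Such change is plausible here. Participants are enrolled because a screening questionnaire classes them as not active, so some rise at a later measurement is expected from regression to the mean. Controls also receive a leaflet and a session advising more activity and less sitting. The trial spans a pandemic suspension, so secular change is possible too.

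Two decisions may rest on the estimate. One is the size of the definitive trial. The other is the efficacy row of Table 1, which needs an effect estimate when the article defines only this one. The order of subtraction adds a second difficulty: benefit takes opposite signs on the two behaviours that the trial targets, while Table 1 reads positive as good.

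**Working it through.** **No figure to reproduce.** The plan is "This trial aims to recruit 60 participants: 30 in the intervention group and 30 in the control group", and the article says that no formal calculation was made. It gives no alpha, power, effect size or SD. The check is therefore the algebra of the stated rule plus an illustration on assumed inputs.

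**Algebra.** Write B and P for the baseline and post-intervention means, with subscripts I (intervention) and C (control).
- Stated estimator: B − P. If computed in the intervention arm, it is B_I − P_I.
- Between-arm effect on change: (P_I − B_I) − (P_C − B_C).
- If both arms change equally, the second quantity is 0 and the first is the whole change with its sign reversed.
- Computing B − P separately in each arm gives two changes; the contrast between them still has to be specified.

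**Sign, with made-up values.**
- Activity rising from 20 to 30 min/day: 20 − 30 = −10. Improvement is negative.
- Sedentary time falling from 600 to 560 min/day: 600 − 560 = +40. Improvement is positive.

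The convention suits outcomes where lower is better (sedentary time, BMI, Timed Up-and-Go) and is reversed where higher is better (physical activity, WEMWBS).

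**Consequence for sample size.** Assumed, not from the article: two-sided 5%, 80% power, 1:1 allocation, one common SD, a standardised change d in the intervention arm, and a control arm that shows a fraction f of that change. The between-arm effect is then d(1 − f), and

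n per arm = 2(1.96 + 0.8416)² / [d(1 − f)]² = 15.70 / [d(1 − f)]².

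| f | n per arm, d = 0.5 | n per arm, d = 0.3 | Power if sized at f = 0 |
|---|---|---|---|
| 0 | 63 | 175 | 80% |
| 0.25 | 112 | 311 | 56% |
| 0.50 | 252 | 698 | 29% |
| 0.75 | 1,005 | 2,791 | 10% |

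For example, d = 0.5 and f = 0.5 gives 15.70 / 0.25² = 251.2, so 252. The requirement grows by 1/(1 − f)².

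**Precision gain from baseline adjustment.** Assumed: correlation 0.6 between baseline and follow-up, complete data, no clustering, and all 60 split 40:20. That split is only an approximation, because participants recruited before the suspension were allocated 1:1.
- Unadjusted follow-up difference: 1.96 × √(1/40 + 1/20) = 0.537 SD.
- Difference in change: 0.537 × √(2 × (1 − 0.6)) = 0.537 × 0.894 = 0.48 SD.
- Baseline-adjusted difference: 0.537 × √(1 − 0.36) = 0.43 SD.

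Since the plan works with change, the relevant gain is from 0.48 to 0.43 SD. It is useful but secondary.

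**The case against.** The best defence is that the sentence describes a first step, done in each arm, with the comparison understood. The Aim is comparative, and Table 1 weighs a confidence interval against a clinically important difference, which suggests a between-arm estimate. That may be what was meant. However, the text labels the before-after quantity itself as the intervention effect and passes it to sample-size planning, and the missing step appears nowhere.

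It is also fair that these are secondary outcomes in a feasibility study, that objective iii is first about variability, and that use for sizing is conditional. This limits the weight of the point. Reporting without significance tests is normal here and is not criticised.

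A reader might infer more than the article supports:
- *That the control arm is never used.* Recruitment, retention, adherence, adverse events and satisfaction are all assessed in both arms, and Table 1 grades adherence to the allocated intervention.
- *That a real gain in activity will be graded Amber.* This follows only if the sign is applied mechanically. Positive and negative in Table 1 can be read as favourable and unfavourable, and the table does not name its primary clinical outcome. Sign has no bearing on sample size, which depends on the squared effect.
- *That the baseline and follow-up means cover different people.* The later visits are optional, so this is a risk, but the article does not say that the baseline mean includes those who do not return. At the post-intervention visit, attempts are made to follow everyone.
- *That no confidence interval is planned.* Table 1 itself commits to one.

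**Conclusion.** The point holds for the effect estimator. As written, it is an uncontrolled change presented as an intervention effect, and it does not match the randomised design that it is meant to summarise. It is a stated rule rather than a detail left to an analysis plan.

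Its size depends on how much controls change, which the article does not give. If they do not change, sample-size planning is unaffected. If they show a quarter to three quarters of the intervention-arm change, a trial sized on the uncontrolled figure would have about 56% down to 10% power instead of 80%. If controls worsened, the error would run the other way. These figures rest on the assumed power, alpha and common SD.

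The sign problem is a matter of definition: the favourable direction in Table 1 is unspecified and differs by outcome under the stated subtraction.

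**What to change.** Replace the sentence that defines the point estimates with text to this effect:

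- The intervention effect is the intervention-minus-control difference at 13 weeks, preferably adjusted for the baseline value of the outcome. A between-arm difference in change, taken as post minus baseline, would also cure the core fault.
- It is reported with a 95% confidence interval that allows for the cluster randomisation of participants recruited before the suspension. A plain analysis of covariance that ignores those clusters could give too narrow an interval.
- The favourable direction is stated for each outcome.
- The same estimate serves the efficacy row of Table 1 and sample-size planning.
- Within-arm changes (post minus baseline) are descriptive only, use participants with both values, and give the number contributing at each optional visit from 6 to 24 months.

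The cost is wording. Baseline and 13-week values are already collected in both arms, and no significance test is added. Allowing for clusters requires the cluster identifier of pre-suspension participants to be kept in the analysis data.

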### Objectives

i.To determine the recruitment, retention and adherence rates in both trial arms and explore reasons for these rates.ii.To determine the acceptability of the intervention in terms of the incidence of adverse events and level of overall satisfaction in both groups.iii.To estimate variability in clinical markers to inform the design of future effectiveness studies (calculate effect sizes for change in physical activity, sedentary behaviour and cardiometabolic risk factors, including BMI and waist circumference).iv.To conduct a process evaluation according to MRC guidance [24] to explore potential mediators of behaviour change (motivation to exercise and psychological needs satisfaction), to determine requirements for clinical staff to deliver the intervention, and service users views of the intervention.

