**Retention**			
**% of recruited patients with follow-up data**	< 65%	65–84%	85–100%

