### Implications of COVID-19 on study delivery

This study is being rolled out during the COVID-19 global pandemic. Therefore, current public health restrictions in place relating to COVID-19 will be followed, aiming to reduce in-person contact with participants to reduce the risk of transmission for patients and staff, where possible (Table 2). Recruitment to the study was open both pre- and post-suspension due to COVID-19; as such, participants recruited to the trial pre-suspension were cluster-randomised in a 1:1 ratio and received an in-person intervention, while participants recruited post-suspension are individually randomised in a 2:1 ratio and receive remote delivery of the intervention as outlined in Table 2.

**Table 2 Tab2:** Proposed protocol changes in response to COVID-19

Study activity	Measures taken
Recruitment	Study information will be shared via email, where possible, or post. Screening visit will be completed via telephone. Consent form will be completed and returned by post or email, where possible. Participants can identify a carer to support them. Carer consent will be obtained. Rolling recruitment will take place as there will be no group component to the intervention and to reduce clinician burden when delivering the intervention.
Randomisation	Participants will be randomised at individual level (due to practicalities of rolling recruitment, e.g. to ensure allocation concealment as participants from the same residential setting may enrol at different times) to either intervention or control group in a 2:1 ratio after completion of the baseline assessment. The allocation ratio was changed to ensure sufficient number of participants are exposed to the intervention and optimal information on intervention delivery can be collected, given that there may be recruitment challenges with remote recruitment and delivery. With 2:1 allocation ratio, two-thirds of participants enrolled will be randomised to the intervention group. Allocations will be undertaken using a permuted block design with unequal block sizes (of 3, 6, 9). A researcher independent of the study will generate the randomisation sequence and allocate the participant after baseline data collection. The randomisation sequence will be concealed from members of the research team involved in participant management to prevent biased allocation [47, 48].

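### The definitive trial is to be sized from effects observed in about 60 people; as defined these are not between-arm differences, and as between-arm differences they are too imprecise to be the target

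*Protocol article*

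**What the plan says.** Three statements in the protocol article's Data analysis section belong together.

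- "Intervention effects will be represented by point estimates and their standard deviations".
- The next sentence defines a point estimate as the baseline mean minus the unadjusted mean at each later timepoint. It names no comparison between arms.
- Then: "These will be used along with their standard deviations to estimate a sample size required for a definitive trial, if appropriate". Because the standard deviations are named separately, the first word can only refer to the point estimates.

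Objective iii agrees. It opens "To estimate variability in clinical markers to inform the design of future effectiveness studies" and then, in brackets, explains this as calculating effect sizes for change in activity, sedentary behaviour and cardiometabolic risk factors.

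On size, Study population states: "This trial aims to recruit 60 participants: 30 in the intervention group and 30 in the control group", and "A formal sample size calculation was not used for this feasibility study". After the suspension the allocation changed: "participants recruited to the trial pre-suspension were cluster-randomised in a 1:1 ratio", whereas "participants recruited post-suspension are individually randomised in a 2:1 ratio".

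A clinically important difference appears only in the efficacy row of Table 1. It has no value there and no link to the sample-size sentence.

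**The concern.** A feasibility trial of this size can give a usable estimate of variability and attrition. It cannot give a usable target difference, for two reasons.

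First, the quantity defined is a change over time. It includes regression to the mean, season and the effect of being measured, all of which also act in the control arm. A randomised comparison must be sized on the difference between arms.

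Second, even a proper between-arm estimate from about 60 people has an error as large as any plausible effect. Required sample size varies with the inverse square of the effect, so that error is magnified. There is also selection. Table 1 makes a favourable efficacy signal part of the progression decision, so the estimates carried forward will tend to be too large.

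Informing a definitive trial is the declared purpose of this study. What is at stake is a main trial whose stated power is not its real power.

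**Working it through.** **Inputs from the protocol.** Target 60, planned 30:30 (Study population). Allocation 1:1 before and 2:1 after the suspension; 2:1 throughout would give 40:20. Table 1 grades retention as the percentage "of recruited patients with follow-up data", with green from 85%: 0.85 × 60 = 51 analysed, which is 34:17 at 2:1 or 26:25 at 1:1. There is no plan figure to reproduce, because the 60 has no formal basis and no main-trial size is given.

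**Assumptions not in the protocol.** True between-arm effect d from 0.2 to 0.5 SD; two-sided 5% test; main trial 1:1 with a 90% power target; no clustering; one population across delivery modes.

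**Step 1: precision of a between-arm difference.** Half-width of the 95% interval, in SD units = t(0.975, df) × √(1/n₁ + 1/n₂).

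- 30:30: 2.002 × 0.258 = 0.52
- 40:20: 2.002 × 0.274 = 0.55
- 26:25: 2.010 × 0.280 = 0.56
- 34:17: 2.010 × 0.297 = 0.60

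An observed 0.3 SD at 30:30 therefore has an interval of −0.22 to 0.82 SD.

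**Step 2: what that does to a sample size.** n per arm = 2(1.960 + 1.282)²/d² = 21.01/d².

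- d = 0.3: 21.01/0.09 = 234 per arm
- d = 0.6: 21.01/0.36 = 59 per arm

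If 0.6 is observed but 0.3 is true, power = Φ(0.3 × √(59/2) − 1.96) = Φ(−0.33) = 37%. Observing 0.6 when 0.3 is true lies well inside the interval in Step 1.

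**Step 3: how often this happens.** Simulation: draw the observed difference and pooled SD, size the main trial on the observed standardised effect when it is favourable, then compute power at the true effect. Ranges run from 30:30 to 34:17. The wrong-direction column can be checked directly as Φ(−d/√(1/n₁ + 1/n₂)).

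| True effect (SD) | Estimate in wrong direction | True power below 80%, favourable estimates | True power below 50%, favourable estimates |
|---|---|---|---|
| 0.2 | 22–25% | 58–61% | 40–44% |
| 0.3 | 12–16% | 49–52% | 26–31% |
| 0.4 | 6–9% | 43–46% | 18–22% |
| 0.5 | 3–5% | 39–42% | 11–15% |

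At a true 0.3 SD with 34:17 analysed, favourable estimates average about 0.39 SD. The implied size runs from about 31 to about 8,900 per arm (5th to 95th percentile), against 234 needed. With an 80% power target and a true 0.3 SD, power falls below 50% in 36–40% of favourable cases.

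**Step 4: the alternative.** Hold the target difference fixed at the true value and take only the SD from this trial. With a 90% target, true power then falls below 80% in about 7–10% of cases, and below 50% in about 0.1% or fewer. Allowing for uncertainty in the SD through its one-sided upper 80% limit multiplies it by √(df/χ²₀.₂): 1.090 at df 58 and 1.099 at df 49. Squared, this is 1.19 to 1.21, so about 20% more participants.

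**The case against.** The sentence ends with a condition and a citation. It could be said that the team may decline the calculation if the estimate is unusable, that the cited method cannot be seen here, and that a definitive trial will need its own justification whatever this article says. Some of this stands. The extreme sizes in Step 3 assume mechanical use, which a sensible team would not follow. But the condition governs whether the calculation is done, not what goes into it, and no other target difference is offered.

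The simulation can also be faulted for using a between-arm difference that the section does not define. That is true, and it is why the literal reading is treated separately. The simulation shows the best case for the sentence.

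Four stronger readings are tempting and not supported:

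- *The main trial would usually be underpowered.* At 0.3 SD it is about half of favourable cases, and fewer at larger effects.
- *The planned size is always too small.* The distribution has a long upper tail, and some plans would be far too large.
- *Objective iii contradicts the analysis.* It asks for effect sizes as well as variability, so the two agree.
- *The SD will be used without regard to its uncertainty.* The article does not say so, and such detail may sit in a fuller document.

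**Conclusion.** The point holds. The protocol names the observed effects as inputs to the definitive trial's sample size, and they are unsuitable on either reading: as written they are not between-arm differences, and as between-arm differences they carry an error of about ±0.5 to 0.6 SD. How often the resulting main trial would be badly underpowered depends on a true effect that the protocol does not give, but the direction is the same from 0.2 to 0.5 SD and at 80% or 90% target power.

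The figures rest on the assumptions listed under the check. They are probably lenient, because the cluster-randomised part and the change from in-person to remote delivery would add uncertainty. The sentence should be changed. The harm lies downstream: recruitment, retention, adherence and acceptability results are not affected, and the error could still be corrected when the main trial is designed.

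**What to change.** Replace the sample-size sentence in Data analysis with wording such as:

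> The main-trial sample size will be based on a prespecified clinically important between-arm difference in the chosen primary clinical outcome, not on the effect observed here. This trial will supply the SD (with its confidence interval, allowing for its uncertainty, for example by an upper confidence limit), the baseline–follow-up correlation and the attrition rate. Observed between-arm effects will be reported with confidence intervals only.

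The upper 80% limit is one convention among several; what matters is that the SD's uncertainty is allowed for. If the main trial is to be cluster-randomised, its size will also need a clustering allowance, which this sentence does not cover.

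The edit is short, but it requires the team to choose the primary clinical outcome and agree an important difference. Table 1 already relies on such a difference without giving its value, so one agreement would serve both places. The planned main trial may be larger, by about 20% if the upper 80% limit of the SD is used. Nothing changes in data collection for the present trial.
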